### Adverse events

Adverse events are defined as symptomatic fracture non-union (three of four cortices not united radiographically at a minimum of 6 months), infection (local infection requiring any treatment), neuropathy, tendon irritation (requiring treatment), tendon rupture or complex regional pain syndrome (diagnosed according to the International Association for the Study of Pain (IASP) clinical diagnosis criteria [31]).

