Significantly lower rates of major complications (including deep infection, reoperation, neuropathy, tendon irritation requiring treatment, tendon rupture, fracture non-union, and implant failure, complex regional pain syndrome, death) at 3 and 12 months post treatmentSuperior (closer to normal) radiographic outcomes (ulnar variance and articular step (millimetres), dorsal angulation and radial tilt (degrees)) at post reduction and 6 weeks or moreSuperior PRWE scores at 3 months, 2, 5 and 10 years to a level of clinical importanceSuperior DASH scores at 12 months, to a level of clinical importance. A difference of greater than 11 points will be considered to be clinically important [33]Superior health-related quality of life (EQ-UI and EQ-VAS scores at 3 months and 12 months, 2, 5 and 10 years to a level of clinical importance. A difference of greater than 0.1 points in the EQ-UI score has previously been used as the minimal clinically important difference (MCID) in orthopaedic surgery [34] and musculoskeletal [35] contexts and will be considered to be clinically important. A difference of 10 on the EQ-VAS has been reported as the MCID and will be considered to be clinically important [36]Lower patient-reported pain (numerical rating scale NRS) at 3 months and 12 months, 2, 5 and 10 years to a level of clinical importance. A systematic review on the MCIDs of Visual Analogue Scales (VAS) used for assessment of acute pain reported that the median MCID was 17 mm on a 100-mm scale [37]. Given that the NRS uses whole integers between 0 and 10, a value of 2 points or greater will be considered to be clinically importantSuperior patient-reported treatment success at 12 months, 2, 5 and 10 years (measured on a 5-point Likert scale)Less patient-rated bother with appearance at 12 months, 2, 5 and 10 years (measured on a 5-point Likert scale)Lower therapy utilisation up to and at 3 months as measured by the prevalence of therapy utilisation at 3 months

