### Statistical analysis

#### Analysis principles

Data will be analysed using statistical analysis package SAS (SAS Institute Inc., Cary, NC, USA) and R statistical computing software [40].

Recruitment for CROSSFIRE concluded in January 2019. The final analysis will commence after the 12-month data collection is complete. The de-identified data-set will be inspected for missing data and data quality.

Study outcomes produce both continuous and categorical data. Continuous data will be inspected for normality. Continuous data will be presented by mean values and standard deviations (SDs) as well as mean difference (MD) and 95% confidence interval (CIs) (see Tables 4 and 5 as examples) if normally distributed, otherwise by median and interquartile range.

**Table 4 Tab4:** Secondary outcomes at 3 months for the randomised group

Outcome		Randomised		
		Surgical (*n*=__)	Non-surgical (*n*=__)	MD (95%CI) or odds ratio (95%CI)
PRWE, mean (SD)				
ED-5D-5L, mean (SD)	EQ-UI			
	EQ-VAS			
Pain on NRS (0-10)				
Patient-reported treatment success n(%)	Very successful			
	Successful			
	Neutral			
	Unsuccessful			
	Very unsuccessful			
Therapy utilisation up to 3 months (Yes/No) n(%)				
Therapy utilisation at 3 months (Yes/No) n(%)				
Radiographic measures, mean (SD)	Dorsal angulation (degrees)			
	Radial tilt (degrees)			
	Ulnar variance (mms)			
	Articular step (mms)

**Table 5 Tab5:** Secondary outcomes at 3 months for the observational group

Outcome		Observational		
		Surgical (*n*=__)	Non-surgical (*n*=__)	MD (95%CI) or odds ratio (95%CI)
PRWE, mean (SD)				
ED-5D-5L, mean (SD)	EQ-UI			
	EQ-VAS			
Pain on NRS (0-10)				
Patient-reported treatment success n(%)	Very successful			
	Successful			
	Neutral			
	Unsuccessful			
	Very unsuccessful			
Therapy utilisation up to 3 months (Yes/No) n(%)				
Therapy utilisation at 3 months (Yes/No) n(%)				
Radiographic measures, mean (SD)	Dorsal angulation (degrees)			
	Radial tilt (degrees)			
	Ulnar variance (mms)			
	Articular step (mms)			

Categorical data will be summarised according to frequency (*n*) and incidence (%) (see Table 5). Comparison between treatment groups will be tested using chi-squared and odds ratio with 95% CI.

Comparisons between treatment groups will be tested at the two-sided, 5% significance level. *P* values will be reported to three decimal places if *P* > 0.001. *P* values < 0.001 will be reported as < 0.001. Means and SDs will be reported to one decimal place.

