### Secondary analysis

Outcomes for the randomised group and the observational group will be analysed and represented separately. Outcomes gathered at 3 months will be displayed for the randomised group (see Table 4) and for the observation group (see Table 5). Outcomes gathered at 12 months will be displayed for the randomised group (see Table 6) and for the observational group (see Table 7). Continuous outcomes will be reported by mean values as well as the MDs and 95% CIs. Categorical outcomes will be reported by frequency, incidence and odds ratios.

**Table 7 Tab7:** Primary and secondary outcomes at 12 months for the observational group

Outcome		Observational		
		Surgical (*n*=__)	Non-surgical (*n*=__)	Mean difference (95%CI)
PRWE				
DASH				
ED-5D-5D, mean (SD)	EQ-UI			
	EQ-VAS			
Pain on NRS (0-10)				
Patient-reported treatment success n(%)	Very successful			
	Successful			
	Neutral			
	Unsuccessful			
	Very unsuccessful			
Patient-reported bother with appearance n(%)	Not at all			
	Bothered a little			
	Bothered moderately			
	Very bothered			
	Extremely bothered			
Radiographic measures, mean (SD)	Dorsal angulation (degrees)			
	Radial tilt (degrees)			
	Ulnar variance (mms)			
	Articular step (mms)			

The MDs of PRWE measured at 3 months between the surgical and non-surgical groups will be tested using two-sample *t* tests. The MDs of DASH measured at 12 months between the surgical and non-surgical groups will be tested using two-sample *t* tests.

Physical therapy utilisation up to and at 3 months will be analysed. If surgical treatment is shown to be superior, a cost-effectiveness analysis will be conducted incorporating therapy utilisation and published separately to this analysis. For the purpose of this analysis, therapy utilisation up to 3 months (Yes/No) and ongoing therapy utilisation at 3 months (Yes/No) will each be reported in terms of frequency, incidence and odds ratio between each treatment group. See Tables 3 and 4 as examples.

Complications will be reported in terms of frequency, incidence and the odds ratio between each treatment group (see Tables 8 and 9 as examples). Odds ratio will be calculated based on the number of participants for whom data is available.

**Table 8 Tab8:** Complications for randomised group

Complication; frequency (incidence)	Randomised group		
	Surgical (*n* = _)	Non-surgical (*n* = _)	Odds ratio (95% CI)
Deep infection	*n* (%)	*n* (%)	
Reoperation	*n* (%)	*n* (%)	
Neuropathy	*n* (%)	*n* (%)	

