## Discussion

This plan describes the statistical analysis for CROSSFIRE. The primary analysis will determine whether surgery is superior to non-surgical treatment with respect to patient-reported wrist pain and function at 12 months. The secondary analyses will determine between-treatment differences at 3- and 12-month timepoints of outcomes including treatment complications and adverse events, patient-reported pain and function, quality of life, therapy utilisation, patient-reported treatment success, patient-reported bother with appearance and radiological outcomes. A sensitivity analysis will be conducted for potential biases, including a comparison between the observation and randomised arms of the study.

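### Complication tables count only deep infection although the adverse-event definition covers any treated infection, and the fixed odds ratio has no provision for sparse or empty rows

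*SAP article*

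**What the plan says.** Two definitions of infection stand in the SAP.

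- **Narrow.** The secondary outcome list (Outcome variables), the secondary hypothesis and the shells for Tables 8 and 9 all name deep infection. The hypothesis reads "Significantly lower rates of major complications (including deep infection, reoperation, neuropathy", and the table row is labelled "Deep infection".
- **Wide.** The Adverse events section counts "infection (local infection requiring any treatment", with no restriction on depth.

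The Discussion says that the secondary analyses will compare "outcomes including treatment complications and adverse events". The only shells for such events are Tables 8 and 9, which have nine named rows and *Any complications*.

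On method, Secondary analysis states "Complications will be reported in terms of frequency, incidence and the odds ratio between each treatment group" and adds "Odds ratio will be calculated based on the number of participants for whom data is available". The general rule for categorical data, under Analysis principles, is "Comparison between treatment groups will be tested using chi-squared and odds ratio with 95% CI". No exact test, zero-cell rule or risk difference is given. Implant failure gets an odds ratio column like every other row.

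**The concern.** Safety is part of the stated purpose of the analyses, and a lower complication rate with surgery is a formal secondary hypothesis. A treated superficial wound infection is an adverse event under one section and has no place in the tables under another. Two analysts following the same plan could code *Any complications* differently. The gap is not symmetrical for this item: only the surgical treatment creates a wound by design, and the Intervention group section describes wound review and suture removal.

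The second problem is statistical. Nine separate rows are to be compared in a trial of 164 randomised participants. For rare events such as tendon rupture, deep infection or death, one arm may have no events. The raw odds ratio is then zero, infinite or undefined. What is reported, and whether it crosses 0.05, would depend on a choice made after the counts are seen.

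**Working it through.** **Inputs.** 164 randomised (Study population), taken as 82 per arm; the equal split is an assumption. The SAP allows for 20% loss: 128/0.80 = 160, which reproduces its target. The same allowance on 164 gives 164 × 0.80 = 131.2, or about 66 per arm. The SAP gives no complication rate, so rates below are assumed and shown as a range.

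**Empty cells.** With the same rate p in both arms and n per arm, P(at least one arm has no events) = 1 − [1 − (1 − p)^n]².

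For p = 0.02 and n = 82: 0.98^82 = 0.191, so 1 − (0.809)² = 0.345.

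| Assumed rate | n = 82 | n = 66 |
|---|---|---|
| 1% | 69% | 77% |
| 2% | 35% | 46% |
| 3% | 16% | 25% |
| 5% | 3% | 7% |
| 10% | about 0% | 0.2% |

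Expected event counts reach 5 per arm only at a pooled rate of 5/82 = 6.1% (5/66 = 7.6%).

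**What a sparse row looks like (82 per arm).**

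- 4 v 0: chi-squared = 164 × (4 × 82 − 78 × 0)² / (82 × 82 × 4 × 160) = 4.10, p = 0.043. Fisher's exact test gives p = 0.120. The raw odds ratio is infinite with no Woolf interval. With 0.5 added to each cell it is (4.5 × 82.5)/(78.5 × 0.5) = 9.5, 95% CI 0.50 to 179.
- 5 v 0: chi-squared p = 0.023, Fisher p = 0.059.
- 0 v 0: neither the odds ratio nor chi-squared is defined.

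**Is chi-squared anticonservative?** Exact null size at a nominal 5%, 82 per arm:

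| Assumed rate | Chi-squared | Fisher |
|---|---|---|
| 1% | 0.8% | 0.02% |
| 2% | 3.2% | 0.25% |
| 3% | 4.4% | 0.75% |
| 5% | 4.2% | 1.7% |
| 10% | 4.9% | 2.9% |

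It is not, on average. The problem is the single sparse table, where the answer depends on the method.

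**Infection gap.** If 2% to 6% of surgical participants had a treated non-deep infection (an assumption), that is 0.02 × 82 = 1.6 to 0.06 × 82 = 4.9, about 2 to 5 people. As an illustration, take *Any complications* at 8 v 8 of 82 (odds ratio 1.00) and add infections to the surgical arm, in participants with no other complication:

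- +2: (10 × 74)/(72 × 8) = 1.28, 95% CI 0.48 to 3.44
- +4: (12 × 74)/(70 × 8) = 1.59, 95% CI 0.61 to 4.11
- +6: (14 × 74)/(68 × 8) = 1.90, 95% CI 0.75 to 4.82

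The point estimate moves; every interval still includes 1.

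**The case against.** The best defence is that two constructs may be intended. The hypothesis speaks of major complications, and the Discussion names complications and adverse events separately. The lists are introduced by *including*, Tables 8 and 9 are offered as examples, and *Any complications* is never defined as the sum of its rows. This stands to a degree: the SAP does not say that treated superficial infections are excluded from the composite. It does not say that they are included either, and nothing reports the wider construct. Nor does a deliberate restriction to severe events fit well, since the same list admits "complications (including deep infection, reoperation, neuropathy, tendon irritation requiring treatment, tendon rupture", where tendon irritation enters on a treatment-required threshold.

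The article condenses a signed full SAP, so sparse-cell handling may be set out there. That softens the methods part but not the conflict of definitions, which lies within the article. Frequency and incidence are reported for every row, so an undefined odds ratio hides no events.

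Some stronger readings are tempting and not supported:

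- **The safety comparison as a whole is tilted towards surgery.** Implant failure, reoperation and deep infection fall mainly or only on operated wrists and count against surgery. A tilt is supported for the infection row alone.
- **The implant-failure cell is structurally zero in the cast arm.** This holds only for participants never operated on. Crossovers analysed as randomised could contribute events. Intention to treat is stated for the primary analysis, and the population for Tables 8 and 9 is not named.
- **Reoperation excludes a first operation after cast treatment.** The term is undefined; an exclusion is not shown.
- **The odds ratios will often be inestimable.** That is likely only at rates of about 1% to 2% or below.

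**Conclusion.** The point holds in two parts. First, the infection definitions conflict, and the wider one has no row or analysis although a comparison of adverse events is promised. This favours surgery on infection only. Its size depends on a superficial-infection rate that the SAP does not give; at an assumed 2% to 6% it concerns about 2 to 5 surgical participants.

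Second, the plan fixes an odds ratio for every complication row, with chi-squared from the general rule, and makes no provision for empty cells. Under equal arms of 82 and equal event rates, a row with a 1% to 2% rate has a 69% to 35% chance of an empty arm. At 5% the chance is 3%, and the composite is unlikely to be touched.

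This should be corrected before unblinding, but it does not threaten the primary analysis.

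**What to change.** 1. Reconcile the infection definitions across Outcome variables, Adverse events, Study hypotheses and Tables 8 and 9. Add a row for infection requiring any treatment, with deep infection as a sub-row, and count it in *Any complications*.
2. For sparse rows, report the risk difference with a score or exact 95% CI and an exact test. Fix in advance what counts as sparse, for example an expected count below 5. Keep the odds ratio for *Any complications*.
3. Present implant failure descriptively among operated participants, without a between-arm odds ratio.
4. Keep the pre-specified reoperation row, but state whether a first operation after cast treatment is counted in it.
5. Name the analysis population for Tables 8 and 9.

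The cost is wording and table shells. The infection row uses events that the adverse-event definition already covers. The reported complication rate would be somewhat higher. Exact tests are also more conservative: at a 2% rate Fisher's null size is 0.25% against 3.2% for chi-squared. For that reason the interval for the risk difference, not the p value, should carry the interpretation.

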### Randomisation and allocation

Randomisation occurred immediately after consent was gained by the recruiting orthopaedic team, within 1 week of the date of the injury. The orthopaedic team member contacted a central computer-based randomisation service by telephone. Participants were randomised using the method of minimisation. Randomisation was stratified by site, and minimisation, adjusting for gender and age (60–74 years and > 74 years), was employed as recommended by the National Health and Medical Research Centre (NHMRC) Clinical Trials Centre which provided the randomisation service.

Given the nature of the comparisons (surgery versus no surgery), it was not possible to blind the surgeon (study) investigators or participants. While this increases the risk of performance and detection bias, every effort was made to ensure that treatment, other than the interventions under study was otherwise identical in both groups. The primary outcome (PRWE score at 12 months) was collected from participants by blinded researchers, by telephone.

The statistician and the investigators conducting the analysis will remain blinded to the treatment groups. The dataset will be de-identified and treatment allocation will be masked using dummy group names (for example, Group A and Group B). De-identification and masking will be performed by an independent investigator who is not associated with the analysis. Masking of treatment allocation will be maintained until the statistical analysis and interpretation has been completed and two versions of the manuscript have been prepared and agreed to by all authors.

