### Data collection

Outcomes are collected at four timepoints; baseline, 3 months, 12 months and 24 months. The timepoints and corresponding outcomes are listed in Table 1. Baseline data is collected by the recruiting clinicians following consent. Baseline data includes age, gender, fracture type (AO/OTA 23A OR 23C), radiographic features of fracture, fracture-healing risk factors (see co-morbidities in Tables 2 and 3) and treatment preference. Paper-based data collection is forwarded to the study coordinator for direct electronic data entry into a central electronic database – REDCap™ [26].

**Table 1 Tab1:** Study outcomes

Baseline measure		Randomised	
		Surgical (*n*=__)	Non-surgical (*n*=__)
Age (years), mean (range)			
Gender n (%)	Female		
	Male		
Fracture type n (%)	23A		
	23C		
Radiographic features, mean (SD)	Dorsal angulation (degrees)		
	Radial tilt (degrees)		
	Ulnar variance (mms)		
	Articular step (mms)		
Co-morbidities, n (%)	Diabetes? (Y/N)		
	Smoker? (Y/N)		
	Glucocorticoid treatment? (Y/N)		
	Osteoporosis treatment? (Y/N)

**Table 2 Tab2:** Baseline characteristics for the randomised group

Baseline measure	Randomised	
	Surgical (*n* = __)	Non-surgical (*n* = __)
Age (years), mean (range)		
Gender *n* (%)		
Female		
Male		
Fracture type *n* (%)		
23A		
23C		
Radiographic features, mean (SD)		
• Dorsal angulation (degrees)		
• Radial tilt (degrees)		
• Ulnar variance (mm)		
• Articular step (mm)		
Co-morbidities, *n* (%)		
• Diabetes? (Y/N)		
• Smoker? (Y/N)		
• Glucocorticoid treatment? (Y/N)		
• Osteoporosis treatment? (Y/N)		

*SD* standard deviation

**Table 3 Tab3:** Baseline characteristics for the observational group

Baseline measure		Observational	
		Surgical (*n*=__)	Non-surgical (*n*=__)
Age (years), mean (range)			
Gender n (%)	Female		
	Male		
Fracture type n (%)	23A		
	23C		
Radiographic features, mean (SD)	Dorsal angulation (degrees)		
	Radial tilt (degrees)		
	Ulnar variance (mms)		
	Articular step (mms)		
Co-morbidities, n (%)	Diabetes? (Y/N)		
	Smoker? (Y/N)		
	Glucocorticoid treatment? (Y/N)		
	Osteoporosis treatment? (Y/N)		

Participants are followed up at 3 months post initial procedure (± 1 week), 12 months post initial procedure (± 1 month) and 24 months post initial procedure (± 1 month). There is an intention to collect outcomes at 5 and 10 years post treatment.

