PRWE gathered at 3 months and 2, 5 and 10 yearsDisability of Arm, Shoulder and Hand (DASH) questionnaire at 12 months. The DASH is a 30-item patient-reported measure of disability and symptoms of the upper limb. It is a continuous score on a scale from 0 to 100 with higher scores indicating poorer outcomes [29]The EuroQol five-dimension five-level questionnaire (EQ-5D-5L), measuring health-related utility-based quality of life at 3 and 12 months and 2, 5 and 10 years. The EQ-5D-5L is a five-dimension patient-reported measure of health-related quality of life (HRQoL) with a separate visual analogue scale (VAS). Distributions of responses to each dimension can be reported categorically; it also produces two continuous variables, a EQ-utility index (EQ-UI) score and a EQ-VAS score. The EQ-UI score is scored on a scale of 0, equating to a health state equivalent to death and 1 equating to full health; it can also take negative values. Given that there are no published Australian normative data on which to calculate EQ-UI scores, UK norms will be used instead. The EQ-VAS score ranges from 0 to 100 with 0 equating to the worst health state imaginable and 100 equating to the best health state imaginable [30]Wrist pain using the numerical rating scale (NRS) at 3 and 12 months and 2, 5 and 10 years. The NRS is a patient-reported 11-point pain scale ranging from 0 to 10 with 0 equating to no pain and 10 equating to the worst possible painPatient-reported treatment success (at 12 months and 2, 5 and 10 years, 5-point Likert scale). The treatment success scale is a non-standard scale. See Additional file 1Patient-rated bother with appearance (at 12 month and 2, 5 and 10 years, 5-point Likert scale). The treatment success scale is a non-standard scale. See Additional file 1Complications (including deep infection, reoperation, neuropathy, tendon irritation requiring treatment, tendon rupture, fracture non-union at 6 months, implant failure, complex regional pain syndrome, death) at 3 months, 12 months, 2, 5 and 10 yearsRadiographic measures (ulnar variance, dorsal angulation, radial tilt, articular step) measured at presentation, post reduction, and between 6 weeks and 12 months)Therapy utilisation up to 3 months (Yes/No) and continuing at 3 months (Yes/No)

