Tendon irritation requiring treatment	*n* (%)	*n* (%)	
Tendon rupture	*n* (%)	*n* (%)	
Fracture non-union at 6 months	*n* (%)	*n* (%)	
Implant failure	*n* (%)	*n* (%)	
CRPS	*n* (%)	*n* (%)	
Death	*n* (%)	*n* (%)	
Any complications	*n* (%)	*n* (%)	

*CI* confidence interval, *CRPS* chronic regional pain syndrome

**Table 9 Tab9:** Complications for observational group

Complication; frequency (incidence)	Randomised group		
	Surgical (*n* = _)	Non-surgical (*n* = _)	Odds ratio (95% CI)
Deep infection	*n* (%)	*n* (%)	
Reoperation	*n* (%)	*n* (%)	
Neuropathy	*n* (%)	*n* (%)	
Tendon irritation requiring treatment	*n* (%)	*n* (%)	
Tendon rupture	*n* (%)	*n* (%)	
Fracture non-union at 6 months	*n* (%)	*n* (%)	
Implant failure	*n* (%)	*n* (%)	
CRPS	*n* (%)	*n* (%)	
Death	*n* (%)	*n* (%)	
Any complications	*n* (%)	*n* (%)	

*CI* confidence interval, *CRPS* chronic regional pain syndrome

Repeated measures analysis will be used for the following:
Continuous variables measured at 3 months and 12 months include EQ-5D-5L (UI and VAS scores), pain on NRS (0–10) and radiographic measures (dorsal angulation, radial tilt, ulnar variance and articular step). These measurements will be analysed using analysis of variance (ANOVA) with repeated measuresCategorical variables measured at 3 months and 12 months include patient-reported treatment success (Likert) and patient-reported bother with appearance (Likert). See Additional file 1 for question format. These variables will be analysed by contingency table to compare the frequency of treatment success categories between the two randomised groups. Results will be displayed as odds ratio with 95% CIs (see Table 4 for example)

The observational group will be used to investigate potential selection bias. Baseline characteristics will be compared between the observational group and the randomised group (see Table 10 for example).

**Table 10 Tab10:** baseline characteristics for the randomised and observational arms of trial

Baseline measure		Randomised arm (*n*=__)	Observational arm (*n*=__)
Age (years), mean (range)			
Gender n (%)	Female		
	Male		
Fracture type n (%)	23A		
	23C		
Radiographic features, mean (SD)	Dorsal angulation (degrees)		
	Radial tilt (degrees)		
	Ulnar variance (mms)		
	Articular step (mms)		
Co-morbidities, n (%)	Diabetes? (Y/N)		
	Smoker? (Y/N)		
	Glucocorticoid treatment? (Y/N)		
	Osteoporosis treatment? (Y/N)		

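### The four radiographic outcomes have a pre-treatment value on the same scale, but the planned comparison leaves it out and so gives up some precision

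*SAP article*

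**What the plan says.** All references are to the SAP article.

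- **Outcome variables** gives the four radiographic measures as "measured at presentation, post reduction, and between 6 weeks and 12 months". The first of these readings precedes treatment.
- **Data collection** treats the presentation readings as baseline: "Baseline data includes age, gender, fracture type (AO/OTA 23A OR 23C), radiographic features of fracture". Tables 2, 3 and 10 tabulate them to describe the groups. No pre-treatment PRWE, DASH, EQ-5D-5L or pain score is listed, so these four are the only outcomes shown with a baseline on their own scale.
- **Secondary analysis** sets the comparison: "Continuous variables measured at 3 months and 12 months include EQ-5D-5L (UI and VAS scores), pain on NRS (0–10) and radiographic measures". The last item is spelled out as "radiographic measures (dorsal angulation, radial tilt, ulnar variance and articular step". The method named is ANOVA with repeated measures. No covariate or change score is mentioned, and the effect is reported plainly: "Continuous outcomes will be reported by mean values as well as the MDs and 95% CIs". Tables 4 and 6 follow that layout.
- **Randomisation and allocation** names the balancing factors: "Randomisation was stratified by site, and minimisation, adjusting for gender and age". Neither displacement nor fracture type is among them.
- **Study hypotheses** includes radiographic superiority of surgery, and **Analysis principles** says: "Comparisons between treatment groups will be tested at the two-sided, 5% significance level". The radiographic comparison is therefore a tested one.

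**The concern.** Initial displacement plausibly predicts final alignment, at least where treatment does not fully remove it. The document gives reasons to expect a wide spread at presentation. Patients qualify on angulation, shortening or articular step, so a patient who qualifies on one measure may be near normal on another. Extra-articular (23A) and complete articular (23C) fractures are both included. In the control group, whatever alignment closed reduction achieved was accepted, with no radiographic threshold.

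If presentation and follow-up values are correlated, a comparison of follow-up values alone has a wider confidence interval than the data allow. Any difference in displacement that arises by chance between the arms is also carried into the estimate in proportion to that correlation. The trial already holds the value needed to correct for it. If the term is not specified before unmasking, adding it once an imbalance has been seen would be a data-driven choice.

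**Working it through.** The plan states no sample size or expected effect for the radiographic outcomes, so there is no radiographic figure to reproduce. Its PRWE target does reproduce, 128/(1 − 0.20) = 160, and is used here only as a source of group sizes.

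**Inputs**
- Randomised: 164 (Study population), or 82 per arm if the arms are equal.
- Planned evaluable for the primary outcome: 64 per arm (Power and sample size). The number with a usable follow-up film is not given, so 64 and 82 serve as a range.
- Correlation ρ between presentation and follow-up value: not in the document. Assumed, 0 to 0.5.

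**Chance imbalance at baseline, in SD units.** The standard error is √(2/n) and the 95% limit is 1.96 × √(2/n).
- n = 82: SE 0.156, limit ±0.31, 20% chance of an imbalance above 0.2 SD.
- n = 64: SE 0.177, limit ±0.35, 26% chance of an imbalance above 0.2 SD.

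**Carry-over into the unadjusted difference** = ρ × imbalance.
- At the 95% limit with 82 per arm: 0.2 × 0.306 = 0.06 SD and 0.5 × 0.306 = 0.15 SD.
- At one standard error: 0.2 × 0.156 = 0.03 SD and 0.5 × 0.156 = 0.08 SD.

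**Gain from adjustment, same ρ in both arms.** The variance is multiplied by 1 − ρ², so the interval narrows by 1 − √(1 − ρ²). Power is for an illustrative true difference of 0.5 SD at 64 per arm.

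| ρ | Variance ratio | CI narrower by | Power |
|---|---|---|---|
| 0 | 1.00 | 0% | 0.81 |
| 0.1 | 0.99 | 0.5% | 0.81 |
| 0.2 | 0.96 | 2.0% | 0.82 |
| 0.3 | 0.91 | 4.6% | 0.84 |
| 0.5 | 0.75 | 13.4% | 0.90 |

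**Different ρ in each arm.** Baseline may matter mainly after casting. This was simulated with 64 per arm, a common fitted slope and 20,000 runs.
- Surgery 0, cast 0.3: variance ratio 0.989, and 1 − √0.989 = 0.6% narrower.
- Surgery 0.1, cast 0.5: variance ratio 0.914, and 1 − √0.914 = 4.4% narrower.
- Zero in both arms: variance ratio 1.008, and √1.008 − 1 = 0.4% wider. That is the price of adjusting for an uninformative covariate.

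In every scenario the adjusted and unadjusted estimates both averaged to the true difference, to within simulation error.

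**The case against.** The strongest reply is that nothing here is an error. An unadjusted comparison of randomised groups is valid, and its 95% interval already allows for chance imbalance. A reader might infer from the missing covariate that the radiographic comparison is biased. The documents do not support that. The estimator is unbiased over repeated randomisation, and what remains is sampling variation conditional on one realised imbalance. This part of the objection stands.

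The second reply is that both treatments realign the fracture, so presentation displacement may predict follow-up only weakly, particularly after plating. This also stands. A reader might take 13% as the expected gain, but that needs a correlation of 0.5 in both arms. It does not fit the argument that baseline matters chiefly in the cast arm, where the gain is much smaller.

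Third, a bare instruction to use ANCOVA would be incomplete. If slopes differ by group and the covariate is not centred, the group coefficient is the difference at a presentation value of zero, which for dorsal angulation would lie far from many eligible patients. For articular step, 23A fractures are extra-articular, so a single linear baseline term may not suit. The follow-up times are also unsettled. These objections are right and shape the fix.

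Finally, the article condenses a fuller plan (v.11) that is not shown and might contain more model terms. But the article does name the method and the time points, and what it names has no baseline term.

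**Conclusion.** The point holds as a modest loss of efficiency in a set of secondary outcomes. The plan collects a same-scale baseline for each radiographic measure, does not balance it at allocation and does not use it in the comparison.

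The likely cost is an interval about 0.5% to 5% wider than it need be if the correlation is weak or confined mainly to the cast arm. It is zero if there is no correlation, and reaches 13% only at 0.5 in both arms. In addition, a realised imbalance at its 95% limit with 82 per arm would stay in the estimate at 0.06 to 0.15 SD for common correlations of 0.2 to 0.5. All of these sizes rest on an assumed correlation.

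A reader might go further and doubt the trial's main result. That does not follow: the primary conclusion rests on PRWE at 12 months, which this point does not touch.

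**What to change.** 1. **Reconcile the follow-up times first.** Outcome variables gives a single window from 6 weeks to 12 months. Study hypotheses refers to post reduction and to 6 weeks or later. Secondary analysis and Tables 4 and 6 assume values at both 3 and 12 months. No model can be fixed until these agree.
2. **Then specify the model before unmasking.** Suggested text: *Each radiographic outcome will be compared between randomised groups by analysis of covariance (or a mixed model if two follow-up films are analysed), with the presentation value of the same measure, centred at its mean over all randomised participants, as covariate. The adjusted mean difference and 95% CI at the average presentation value will be reported, with the unadjusted difference alongside.*
3. **Use the presentation value.** The post-reduction value follows treatment and should not be a covariate.
4. **Articular step.** Add fracture type (23A or 23C) to the model, or restrict this analysis to 23C.
5. **Missing presentation films.** State a simple baseline imputation so that participants without a readable film remain in the intention-to-treat analysis.

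The cost is a few sentences in the plan and a covariate already planned for collection. If the presentation value turns out to be uninformative, the loss is about 0.4% in interval width at 64 per arm.
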